## 2. WORKING HYPOTHESIS AND PROPOSAL

We propose to use autologous transplantation of fecal microbiota to AML or HR MDS patients treated with intensive chemotherapy and antibiotics in order to restore the balance of their intestinal microbiome and thereby eradicate treatment-induced MDRB, infection-related complications, as well as sequelae to the gastrointestinal tract. Therefore, we propose to perform a single-arm multicentre prospective FMT trial in AML or HR MDS patients receiving intensive chemotherapy, and who are usually heavily treated with broad-spectrum antibiotics during aplasia that generate a profound status of dysbiosis. For this purpose, at the time of admission and diagnosis, patients will be requested to donate stools that will be comprehensively screened, and if deemed appropriate according to protocol criteria, conditioned and stored frozen until future processing and transplantation after aplasia completion.

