***D29 (between D24 and D34, depending on patient’s condition) – Visit 2 – Faeces analysis for dysbiosis characterization***

After aplasia completion ,faeces and blood will be collected by caregivers within 3 days before antibiotics discontinuation (around Day 29) (**Procedures will be provided by BIOFORTIS SAS**) for biochemical assay, bacteriology (detection of MDRB and *C. difficile*), determination of dysbiosis using metagenomic analysis and analysis of blood immune cells. Detection of MDRB and/or *C. difficile* will not constitute a criterion for exclusion but will allow the measure of the potential impact of chemotherapy and antibiotherapy on the emergence of these bacteria. The patient will fulfil the EQ-5D-5L questionnaire to evaluate its gastrointestinal symptoms and its quality of life. The patient is next prepared for the following AFMT according to the procedure (**Appendix 1**).

|                                                                                                         |                      |                                                                                               |
|---------------------------------------------------------------------------------------------------------|----------------------|-----------------------------------------------------------------------------------------------|
| [figure not shown]
MaaT Pharma | Protocol             | Protocol N°: MPOH02
EudraCT N° : 2015-004335-12
Version 10.0
Date : 20 November 2017 |
|                                                                                                         | ODYSSEE STUDY |                                                                                               |

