| Calprotectin, neopterin, zonulin, secretory IgA on faeces                                                                                                                                                                           | Genetic sequencing of bacterial genes (shotgun: all metagenome sequencing)
Diversity index of bacterial microbiota
Dysbiosis characterization                                           |
| BLOOD ANALYSIS                                                                                                                                                                                                                      |                                                                                                                                                                                               |
| Monitoring of blood immune cells                                                                                                                                                                                                    |                                                                                                                                                                                               |

Table 3: List of analyses requested for the study

The patients will be followed for assessment of study endpoints and recording adverse events that could happen after intervention until the end of the hospitalization for consolidation chemotherapy. All clinical severe events will be recorded in the CRF during any patient transfer to other site or service (Emergency care). Information of type, dose, duration of antibiotherapy, immunotherapy and chemotherapy will be given to explore the possible correlation between treatments, dysbiosis status and its severity. Relationship of adverse events to AFMT will be assigned by the investigator with the help of the data. All serious adverse reaction will be reported according to the regulatory procedure of adverse reaction declaration.

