### **7.2.2. Effect of dysbiosis correction on patient clinical status**

Previous researches provided some evidence of the association between the observed disorder or disturbance of the normal microbiota and the patient health status, infectious and digestive status. In the following, we call these variables Health Status Related HSR variables. In particular, one of them is the MDRB measured at each visit of the trial. For simplification of description of the following development, we keep the general term HSR to represent any health-status related variable measured, although the MDRB reduction will constitute the most important endpoint among any possible HSR.

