### 7.3.3. Secondary analyses : Association between S and health status

The assumed hypothesis is that the deterioration of the microbiota (MB) is associated with patient health status. In what follows, we consider one variable H in particular among the candidate HSR set, with  $H_b$ ,  $H_d$  and  $H_f$  designating the three values measured at baseline, deterioration and final times, respectively. Let us consider the following model:

$$H_i = k_0 + k_b.H_{i-1} + k_c.S_i + \eta_{i,\text{center}} \quad \text{for } i=b,d,t \quad [1]$$

|                                                                                                         |                      |                                                                                               |
|---------------------------------------------------------------------------------------------------------|----------------------|-----------------------------------------------------------------------------------------------|
| [figure not shown]
MaaT Pharma | Protocol             | Protocol N°: MPOH02
EudraCT N° : 2015-004335-12
Version 10.0
Date : 20 November 2017 |
|                                                                                                         | ODYSSEE STUDY |                                                                                               |

This model is a mixed model by considering the 3 measurements correlated within the patient random factor. The estimates are  $k_0$ ,  $k_b$ ,  $k_c$ , and the standard deviation  $\eta$ . This model assumes the instantaneous association between the MB diversity  $S$  and the health status, and tests the existence of an association between  $H$  and  $S$ , however, without possibility to test either relationship  $H \rightarrow S$  or  $S \rightarrow H$ .

However, this model can be tested in two different ways:

$$H_{i+1} = k_0 + k_b.H_i + k_c.S_i + \eta.\text{center} \quad \text{where for } i=b,d,t \quad [2]$$

In this model [2], health status (HS) at time  $(i+1)$  is assumed dependent on MB diversity at time  $i$ . This model will test the effect of MB diversity as a directional effect of lag=1 on HS, in other words, MB status affects HS with some delay, such result providing some evidence of a causal effect of MB on HS.

Another formulation should be

$$S_i = k_0 + k_b.S_{i-1} + k_c.H_{i-1} + \eta.\text{center} \quad \text{where for } i=b,d,t \quad [3]$$

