In this model [3], health status at time  $(i)$  is assumed to affect MB diversity at time  $i+1$ . This model will test the effect of HS effect as a directional effect of lag=1 on MB diversity. In other words, HS status affects MB with some delay, such result providing some evidence of a causal effect of  $HS \rightarrow MB$ .

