### **7.5.2. Inferential Aspects**

We plan to conduct an Individual Patient Meta-analysis (IPDM) aiming at assessing the AFMT effect compared with no treatment in recovering the initial MB previously deteriorated by medication.

The inferential model will be:

$$HR_i = k_0 + k_b.H_i + k_c.S_i + k_t.FMT + \eta.center \quad \text{where for } i=b,d,t \quad [4]$$

This model is similar to [1] except that a treatment effect (FMT) is coded 1 or 0, following that the patient has been administered AFMT (in this study) or not (in the observational study). As the decision to treat or not has not been randomized and originates from two separate studies, the comparison between baseline values of the two studies will identify variables  $X_i$  for which differences were identified on the two studies, and the used model will be adjusted for these variables as shown in the following model [5]

$$HR_i = k_0 + k_b.H_i + k_c.S_i + k_t.FMT + \eta.center + \sum w_i X_i \quad \text{where for } i=b,d,t \quad [5]$$

The above mentioned models [2] and [3] assessing the direction of the effect HS-S will be conducted by adding the main treatment (FMT) effect.

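### Section 7.3.3 reads lag-1 coefficients as evidence of causation, but no model from [1] to [5] includes antibiotic exposure, a recorded cause of dysbiosis on the protocol's own account

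*Protocol*

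**What the plan says.** Section 7.3.3 sets out three models for a health variable H and diversity S, measured at baseline (b), deterioration (d) and final (f) times. Model [1] relates H and S at the same visit, and the protocol states that it cannot show direction. Model [2] is lagged: "H_{i+1} = k_0 + k_b.H_i + k_c.S_i", plus a centre term. A finding from it is described as "such result providing some evidence of a causal effect of MB on HS". Model [3] reverses the roles, and the text says of it that "HS status affects MB with some delay, such result providing some evidence of a causal effect". Section 7.2.2 says which H matters most: "the MDRB reduction will constitute the most important endpoint among any possible HSR".

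Section 7.5.2 pools the trial with the observational ULYSSE study. Model [4] adds an FMT indicator. Model [5] adds covariates chosen by this rule: "the comparison between baseline values of the two studies will identify variables".

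On antibiotics, section 2 describes the patients as "heavily treated with broad-spectrum antibiotics during aplasia that generate a profound status of dysbiosis" and calls the MDRB treatment-induced. The Visit 2 text in section 6.4.2 says that MDRB detection "will allow the measure of the potential impact of chemotherapy and antibiotherapy on the emergence of these bacteria". Table 2 (section 6.4.3.1) lists curative and prophylactic antibiotics with molecule, dose, duration and dates among the data recorded. Their stated use is in section 6.4.3.2: "Information of type, dose, duration of antibiotherapy, immunotherapy and chemotherapy will be given to explore the possible correlation between treatments, dysbiosis status" and its severity.

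**The concern.** On the protocol's own account, antibiotics lower diversity and contribute to MDRB. Exposure differs between patients at the same visit, because duration and choice of antibiotics vary with the course of aplasia. It is thus a candidate common cause of S and H. Lagging S does not remove a cause that acts before the deterioration sample and carries forward to the final visit. A visit term does not remove it either, because the variation is between patients.

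The stake is interpretation. The protocol fixes both the formula and its causal reading. If the S coefficient in model [2] is significant because heavily treated patients have both low diversity and worse later health, following the text leads to reporting evidence that the microbiota drives health. Model [3] has the same weakness in the other direction.

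**Working it through.** **1. Terms in each model.**

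| Model | Terms | Antibiotic term |
|---|---|---|
| [1], [2] | intercept, previous H, S, centre | none |
| [3] | intercept, previous S, previous H, centre | none |
| [4] | intercept, H, S, FMT, centre | none |
| [5] | as [4], plus variables that differ at baseline | cannot enter: induction antibiotics come after D0 |

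**2. Where model [2] gets its information.** Section 7.1.1 expresses S as a ratio to baseline. On that scale the baseline value is 1 for every patient, so the b-to-d step carries no information on S and the d-to-f step carries it all. The deterioration stool is taken within 3 days before antibiotics stop (section 6.4.2, Visit 2), when the imprint of antibiotics on S should be close to its greatest.

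**3. Set-up.** The documents state no strength for any link, so there is no plan figure to reproduce and every strength below is an assumption. Let A be antibiotic exposure before the deterioration stool, with A, S, Hd and Hf standardised and higher H meaning better health:

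- S = −a·A + noise
- Hd = −0.3·A + noise
- Hf = 0.4·Hd − c·A + noise, with no effect of S.

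Here a is the A–S correlation in magnitude, and c is the direct effect of earlier antibiotics on final health beyond Hd.

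**4. Size of the spurious coefficient.** Regressing Hf on Hd and S without A, the population coefficient on S is

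k_c = c·a·(1 − 0.3²) / (1 − a²·0.3²).

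- a = 0.3, c = 0.3: 0.09 × 0.91 / 0.9919 = 0.083
- a = 0.5, c = 0.5: 0.25 × 0.91 / 0.9775 = 0.233
- a = 0.7, c = 0.6: 0.42 × 0.91 / 0.9559 = 0.400
- c = 0, any a: 0

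The last line is decisive. If antibiotics reach final health only through Hd, model [2] already blocks the path by conditioning on Hd.

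**5. Rejection rates.** Ordinary least squares, two-sided 5% test of k_c, true effect zero, n = 20, d-to-f step, 10,000 simulated trials per row:

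| a, c | Without A | With A as covariate |
|---|---|---|
| 0.3, 0.3 | 0.068 | 0.052 |
| 0.5, 0.5 | 0.211 | 0.051 |
| 0.7, 0.5 | 0.386 | 0.050 |
| 0.7, 0.6 | 0.567 | 0.050 |
| 0.5, 0 | 0.050 | 0.047 |
| 0.7, 0 | 0.053 | 0.048 |

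A separate run of 4,000 trials per row gave 0.057, 0.221, 0.402 and 0.571 for the first four rows. More patients do not help: at n = 60 the same four rows gave 0.104, 0.570, 0.870 and 0.977 unadjusted.

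**6. Direction.** The spurious sign is not fixed. When the b-to-d and d-to-f steps were stacked with S left unscaled, the coefficient was negative and the test rejected in 7 to 23% of runs.

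**7. Model [3].** The argument is symmetric. If induction antibiotics act on final diversity beyond diversity at deterioration, the coefficient on previous H is biased in the same way.

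**The case against.** Much of the case on the other side stands.

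- **Antibiotics are not the only cause.** Section 1.4 says chemotherapy alone can change the microbiota, and the Visit 2 text names both for MDRB. Antibiotics are one cause among others.
- **The error is possible, not certain.** A reader might infer from same-visit simulations, which reject in about a third of trials at correlations of 0.5, that the causal sentence fails at that rate. Those rates belong to model [1], for which the protocol disclaims direction. When exposure is drawn afresh at each visit with no carry-over, model [2] rejects about 5% of the time.
- **The pooled analysis is already guarded.** A reader might infer that a difference in antibiotic use between the studies would be credited to AFMT. Section 7.5.4 states that study and treatment are confounded and that no treatment effect can be concluded. Nor does a simple two-group comparison of S correspond to models [4] or [5], which have a health outcome and condition on S.
- **The simulated H is continuous.** The leading H is MDRB. Carriers at D0 are excluded, and section 7.1.2 considers a pre-AFMT prevalence of 0.15 to 0.20, or 3 to 4 of 20 patients. The simulation shows the mechanism, not the error rate for that endpoint.
- **The models are secondary and exploratory,** the wording claims only some evidence, and a SAP could add covariates. But section 7.3.3 does not leave these models to the SAP, as section 7.2.1, the survival analysis and section 7.5.3 do for theirs. It writes the formulas and the reading itself.

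**Conclusion.** The point holds in a limited form. Antibiotic exposure is absent from all five models and is excluded from model [5] by its selection rule, although the protocol treats it as a cause of dysbiosis and MDRB and records it in usable detail. The causal reading of models [2] and [3] is therefore unsupported as written, and a significant S coefficient could reflect prior antibiotic exposure.

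The size is unknown. In the illustration, the 5% test in model [2] rejects at about 7%, 21 to 22% and 57% under weak, moderate and strong assumed links, and only if earlier antibiotics act on later health beyond Hd. Without that direct effect, or with antibiotic exposure in the model, it rejects at about 5%. The documents do not support saying that a false causal finding will occur, that its direction is known, or that the ULYSSE comparison would be reported as an AFMT effect. The analyses are secondary, but the correction is cheap and should be made.

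**What to change.** 1. In section 7.3.3, describe results from models [2] and [3] as temporal associations and drop the causal wording.
2. In the d-to-f step of models [2] and [3], add days of systemic antibiotics between D0 and the D29 stool as a covariate, at least in a sensitivity analysis. This exposure precedes AFMT and falls before the deterioration sample.
3. In section 7.5.2, allow the same pre-AFMT value into the adjustment set of model [5], alongside variables that differ at D0. Section 7.5.1 says ULYSSE takes the same measurements; confirm that this includes antibiotic dates.
4. Do not adjust for antibiotic use after AFMT. Section 4.4 lists it as an outcome of dysbiosis correction, so conditioning on it could remove part of the effect under study. Time from last dose to stool is not a useful D29 covariate either, because that stool is taken before antibiotics stop.

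The cost is a wording change and one variable derived from recorded data. With 20 patients, and leaving centre aside, the residual degrees of freedom for the d-to-f step fall from 20 − 3 = 17 to 20 − 4 = 16. Confounding by chemotherapy and by other aspects of illness severity would remain, which is why the wording change is needed even with the covariate.

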### Free survival analysis

Global survival and free survival disease at day 70 (+/- 10 days) and 12 months after inclusion will be analyzed by Kaplan-Meier analysis and other survival analysis for comparison: log-rank and cox proportional hazard regression models. These analyses will be described in detail in the Statistical Analysis Plan.

## **7.4. Interim analyses**

### **7.4.1. Interim analysis**

An interim analysis will be performed after the inclusion of 9 to 12 patients and will analyze data collected until the main follow-up completion (70 days after patient's inclusion).

|                                                                                                         |                      |                                                                                               |
|---------------------------------------------------------------------------------------------------------|----------------------|-----------------------------------------------------------------------------------------------|
| [figure not shown]
MaaT Pharma | Protocol             | Protocol N°: MPOH02
EudraCT N° : 2015-004335-12
Version 10.0
Date : 20 November 2017 |
|                                                                                                         | ODYSSEE STUDY |                                                                                               |

In this study, the measurement of clinical relevance is based on the standardized mean difference or cohen effect size. Although a cut-off value of Standard Mean Deviation SMD >0.5 is widely admitted for controlled trials, the observed standard deviation should be larger than expected and the SMD should underestimate the clinical relevance. Similarly the correlation  $R (St, Sf)$  is unknown and may strongly impact the power of the study. In these conditions, interim analyses will aim at an estimate of  $R (St, Sf)$  and the standard deviation, and may help to reconsider the sample size, should these values be different from the assumed values when calculating the power. The interim analysis will be conducted accordingly to the rules described in DSMB Charter.

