**Supplementary Table 9. Reasons for screening failure (n=37).**

|                                                          |                                                                                        |
|----------------------------------------------------------|----------------------------------------------------------------------------------------|
| Related to IMP manufacturing
n=22 (59%) | Insufficient raw material; n=14 (38%)                                                  |
|                                                          | Logistic failure; n=4 (11%)                                                            |
|                                                          | Quality control for batch release not reached; n=4 (11%)                               |
| Related to the patient
n=15 (41%)       | FMT not performed due to patients' condition; n=5 (14%)                                |
|                                                          | Patient's refusal to collection of the inoculum procedure (consent withdraw); n=3 (8%) |
|                                                          | AML diagnosis not confirmed; n=1 (3%)                                                  |
|                                                          | MDRB or C. difficile carriage at diagnosis; n=6 (16%)                           |

IMP: Investigational Medicinal Product; FMT: Fecal Microbiota Transfer; AML: Acute Myeloid Leukemia; MDRB: Multi-Drug Resistant Bacteria

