### **6.2. Study duration**

Total duration of the study: 24 months

Inclusion period: Maximum 12 months (estimation)

The inclusion period will continue until the recruitment of 20 transplanted (AFMT) patients.

Participation period for a patient: Main period ≈ 70 days

Follow-up period: 1 year

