### **6.3. Number of patients included in the study- Recruitment potential**

Number of AML/ HR MDS patients: 20

All documentation of **MaaT Pharma** is PROPRIETARY information and may not be forwarded to third parties without prior written consent from **MaaT Pharma**. Reproductions, either in part or in whole, may not be published or copied in any manner, without the explicit written consent of **MaaT Pharma**

|                                                                                                         |                      |                                                                                               |
|---------------------------------------------------------------------------------------------------------|----------------------|-----------------------------------------------------------------------------------------------|
| [figure not shown]
MaaT Pharma | Protocol             | Protocol N°: MPOH02
EudraCT N° : 2015-004335-12
Version 10.0
Date : 20 November 2017 |
|                                                                                                         | ODYSSEE STUDY |                                                                                               |

Recruitment of patients is estimated around 1 per month and per centre.

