#### **6.4.2. Conduct of the study**

##### **Day 0- Visit 1- Inclusion**

Patient diagnosed with AML/ HR MDS will be asked to participate in this study by the investigating physician during his hospitalization for the treatment of AML/ HR MDS or during a consultation at day hospital before hospitalization. Prior to the initiation of any intensive chemotherapy and any antibiotherapy, the patient will be examined during a consultation by the physician to ensure that the patient fulfils inclusion and non-exclusion criteria (with the help of a questionnaire in **Appendix 3**). The patient will be enrolled in the study after receiving oral and written information and giving his consent (**Appendix 4**). Clinical and biological tests (cf table 2) will be performed as part as the normal patient care. Moreover, several microbiological analyses, selected according to ANSM recommendations and required for the study will be performed on the patient's faeces, collected with the help of a caregiver in special containers and following procedures provided by the sponsor. Collection of faeces and blood will be done as soon and as simultaneously as possible after patient's inclusion and before any chemotherapy. If needed, faeces can be collected at patient's home, before hospitalization. In that case, special containers will be provided and procedure will be explained to the patient during consultation. An user manual will also be provided. Blood sample will be collected at hospital admission.

All analyses performed on faeces and blood are:

- Research of MDRB (Methicillin-resistant *Staphylococcus aureus* (MRSA), Vancomycin- and glycopeptid-resistant enterococci (VRE, GRE), Extended-spectrum- $\beta$ -lactamase (ESBLs) producing Gram-negative bacteria, carbapenemase-producing bacteria)
- Research of pathogenic bacteria (*Campylobacter sp.*, *Listeria sp.*, *Salmonella sp.*, *Shigella sp.*, *Vibrio sp.*, *Yersinia sp.*, Toxin+ *C. difficile*)
- Research of parasites (Strongyloides stercoralis, Cryptosporidium, Cyclospora, Isospora, Entamoeba histolytica, Giardia intestinalis, Microsporidia, Dientamoeba fragilis, Blastocystis fragilis).

Microbiological analysis will be performed in BIOFORTIS SAS according to standard operating procedures (SOP) of the laboratory. Detection of MDRB, *C. difficile*, pathogenic bacteria, parasites, norovirus and/or rotavirus in the stool collected during the inclusion visit is an exclusion criterion of the study.

---

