#### **7.4.2. Futility analysis**

A one-stage futility stopping will be based on conditional power (CP), the probability to detect a significant result at the end of the study, given the results observed at an intermediate time. This analysis is planned after a possible adaptation of sample size. CP will be estimated through B-values (85, 86).

This analysis will be carried out when at least 40% of the planned sample are available, and futility threshold will be  $CP_{min} = 0.10$  involving a slight increase of type 2 error ( $\beta = 0.1/0.9 = 0.111 - 0.10 \cong 0.01$ ) (87). None of these interim analyses require a type-I adjustment. Further details will be described in the Statistical Analysis Plan (SAP) as appropriate.

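### The interim in section 7.4.1 is triggered by inclusions, not by transplanted patients with paired results, so it sets no minimum of the information it needs

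*Protocol*

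**What the plan says.** - **Interim trigger (section 7.4.1):** "An interim analysis will be performed after the inclusion of 9 to 12 patients". The same sentence says that data up to the end of main follow-up, 70 days after inclusion, will be analysed.
- **Purpose (section 7.4.1):** the interim is to estimate R "and the standard deviation, and may help to reconsider the sample size, should these values be different from the assumed values when calculating the power". On procedure: "The interim analysis will be conducted accordingly to the rules described in DSMB Charter". The charter is not among the documents at hand.
- **Meaning of inclusion (section 6.4.2, Day 0, Visit 1):** "The patient will be enrolled in the study after receiving oral and written information and giving his consent". Stool is screened after that. The physician decides on AFMT eligibility during induction, and transplantation follows at about Day 30.
- **Recruitment stop (section 6.2):** "The inclusion period will continue until the recruitment of 20 transplanted (AFMT) patients".
- **Study size (section 6.3, whose title refers to patients included):** "Number of AML/ HR MDS patients: 20". The synopsis likewise gives 20 subjects.
- **Futility look (section 7.4.2):** "This analysis will be carried out when at least 40% of the planned sample are available".
- **Losses between inclusion and AFMT:** section 5.2 lists exclusions that can arise only after the inclusion visit, namely a positive stool screen, ineligibility shortly before transplantation, and an inoculum that cannot be used. No expected rate is given.

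**The concern.** Sections 6.2 and 6.3 give the same number, 20, in different units. The two agree only if every included patient is transplanted, and section 5.2 shows that the plan does not expect this. Section 7.4.1 then counts its trigger in the earlier unit, inclusions.

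This matters because of what the interim is for. R and the SD concern the post-induction value Sd and the post-AFMT value Sf, each taken relative to baseline (section 7.1.1). A patient who leaves before AFMT contributes no post-AFMT value and therefore no pair. Followed as written, the trigger could be met with very few pairs in hand, and the DSMB would be asked to keep or change the sample size on estimates that cannot support either choice.

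**Working it through.** **1. The planning figures that the interim would revisit.** Section 7.1.1 assumes R = 0.5 and a difference of 0.5 SD, with 30 patients and one-sided alpha 0.05. The SD of the difference, in units of the common SD, is √(2(1 − 0.5)) = 1. The normal-approximation power is Φ(0.5√30 − 1.645) = 0.863, close to the stated 0.875. The later table in section 7.1.2 gives 20 patients at effect size 0.6 and beta 0.25. A two-sided 5% normal formula reproduces it: ((1.960 + 0.674)/0.6)² = 19.3, rounded up to 20. Both results depend directly on the SD, and the first also on R.

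**2. What inclusion means in section 7.4.1.** The trigger sentence itself counts 70 days from inclusion. That is Visit 4 (D70) counted from Day 0, so inclusion there is the Day 0 visit. Supplementary Table 1 also reports age at inclusion for the 37 screen-failed patients, so the trial's own tables treat them as having been included.

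**3. Transplanted patients among 9 to 12 inclusions.** Expected number = inclusions × yield.

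| Yield | Source | From 9 | From 12 |
|---|---|---|---|
| 80% | assumption | 7.2 | 9.6 |
| 60% | assumption | 5.4 | 7.2 |
| 25/62 = 40.3% | results tables | 3.6 | 4.8 |

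The last row uses 25 treated patients (Supplementary Table 2) and 37 screen failures (Supplementary Table 9). The total 25 + 37 = 62 is a sum and is not stated in the document. The exact 95% interval for 25/62 is 28% to 54%. This is a trial result, not a planning figure, and serves only as an illustration.

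Patients with usable samples would be fewer. Supplementary Figure 3 shows 18 patients with complete Visit 1 to Visit 3 samples. On that count 18/62 = 29.0%, which gives 2.6 from 9 inclusions and 3.5 from 12.

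**4. Precision from n pairs.** For an estimated R of 0.5, the Fisher interval is tanh(0.549 ± 1.96/√(n − 3)). For the SD, the limits as multiples of the estimate are √((n − 1)/χ²) at the 97.5% and 2.5% points on n − 1 degrees of freedom.

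| Pairs | 95% interval for R | SD multiples |
|---|---|---|
| 4 | -0.89 to 0.99 | 0.57 to 3.73 |
| 5 | -0.68 to 0.96 | 0.60 to 2.87 |
| 9 | -0.25 to 0.87 | 0.68 to 1.92 |
| 12 | -0.10 to 0.83 | 0.71 to 1.70 |

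**5. Effect on a sample-size review.** For a fixed difference, the required number scales with SD². Around a re-estimate of 20, the limits with 4 pairs are 20 × 0.57² ≈ 6 and 20 × 3.73² ≈ 278. With 12 pairs they are 20 × 0.71² ≈ 10 and 20 × 1.70² ≈ 58.

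**The case against.** The best case for the plan is that 9 to 12 simply means 9 to 12 of the planned 20, that is 45% to 60%. This fits the exploratory look from 12 patients in section 7.1.2 and the 40% futility fraction. Patients analysed to Day 70 would already have passed AFMT and Visit 3. Section 5.2 also lists failure to reach transplantation among the exclusion criteria, so such patients might not be counted at all. Finally, the DSMB Charter governs the interim and may settle the unit. This stands to the extent that the shortfall is conditional. It does not remove the problem, because the protocol's own trigger names inclusion, which it places at Day 0, and sets no minimum number of pairs.

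It is also fair that imprecision is not due to the counting unit alone: 9 to 12 pairs leave R poorly estimated, as expected in a 20-patient pilot.

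Three stronger readings are tempting and are not supported:

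- **That the plan would yield only 4 to 5 evaluable patients.** The 40% yield was known only afterwards, and the 3.6 to 4.8 are transplanted patients, not evaluable ones.
- **That the futility look is defeated.** Section 7.4.2 has its own trigger, based on the share of the planned sample available, and does not run on the inclusion count.
- **That recruitment would end at 20 inclusions.** Section 6.2 states the stopping rule in transplanted patients.

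**Conclusion.** The point holds as a defect in the stated trigger. Section 7.4.1 counts patients at a stage before they can supply the information the interim is meant to use, and it fixes no minimum amount of that information. Sections 6.2 and 6.3 need to be brought to the same unit.

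The size depends on an unstated yield. At an assumed 60 to 80%, the interim would hold about 5 to 10 transplanted patients. At the rate later observed it would hold about 4 to 5, with fewer having complete samples. At the low end R is essentially unknown and the upper SD limit is 2.9 to 3.7 times the estimate, so a sample-size review would be uninformative. With 12 pairs the review is better founded but still weak. The conclusion assumes that inclusion carries its Day 0 meaning and that the charter does not already set a different unit.

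**What to change.** - **Section 7.4.1:** trigger the interim when 9 to 12 patients have received AFMT and have paired Visit 2 and Visit 3 diversity results. Check that the DSMB Charter says the same.
- **Section 6.3 and the synopsis:** give the study size as 20 transplanted patients, to match section 6.2.
- **Section 7.4.2:** express the 40% fraction in the same unit, 0.40 × 20 = 8, so at least 8 of 20 transplanted patients with paired results.

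The cost is a change of wording in the protocol, and in the charter if it differs, and an interim that falls somewhat later in calendar time. The planned number of treated patients does not change. The change removes the avoidable part of the imprecision; it does not make R precise at 9 to 12 pairs, and any sample-size decision taken then should be read with that in mind.
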